### **9.2 Analysis**

Only men who provided a foreskin sample will be included in analysis. Men who withdraw prior to circumcision will be replaced (see section 6.5). Primary groups for comparison will be men who received the same PrEP drug and dose, with no post-exposure drug, as indicated in Figure 1 (Groups A, B, C, D), pooled across the two sites. This means that data from men who received the same PrEP drug and dose, but differed in time between last dose and circumcision, will be

combined into a single group for analysis. If there is a cause to suspect that one of the timings was not effective (i.e. that the timing fell outside the effective window of the treatment regimen) then the groups will also be analysed according to randomisation groups (2-9).

Analyses will be descriptive. The primary analysis will use the result from a p24 antigen assay; p24 antigen level at day 15 after ex vivo HIV exposure; slope of p24 antigen level (day 3 to day 15) and area under the curve (day 3 to day 15).

To evaluate in vitro dosing FTC-TDF and FTC-TAF, analysis will be within randomisation groups - that is, men who received the same oral PrEP dosing. The results from foreskin tissue exposed to in vitro drug will be compared to tissue which was not exposed within an individual. All analysis will be descriptive

only; we will report results in each group, and 95% confidence intervals.

The analysis plan for estimating the pharmacodynamic dose-response curves will follow previously described methodology. The dose-response relationships between percentage protection and time since drug initiation and drug discontinuation following steady state will be generated for each drug. In addition, the relationship between pharmacokinetic parameters (concentrations of drug in rectal fluid, foreskin and plasma), pharmacodynamic outcomes, cellular activation and microbiome will be evaluated.

All demographic (age, height, weight, BMI, ethnic origin, etc.), clinical (physical examination, medical history, concomitant diseases) characteristics and survey responses will be tabulated and analysed descriptively by country.

Quantitative data generated from the socio-behavioural, willingness to participate and exit survey will be analysed using Statistical Analysis Software (SAS), Statistical Package for the Social Sciences (SPSS) or Stata. Preliminary analyses will include checks for missing values, data range, and outliers. Normality will be examined using Q-Q plots and continuous data will be assessed for transformations or categorizations. Bivariate analyses will include Chi-square and Fisher's Exact tests to compare categorical variables, and T-tests or Wilcoxon tests for continuous variables. Descriptive statistics by site will be used to describe the study sample, and assess factors associated sexual behaviour, PrEP acceptability and clinical trial feedback/experience. The precise definition of outcomes will be defined during the formative research.

Qualitative data will be organised and managed using a common method of analyses using software or manual methods, depending on the site. Data analysis from the IDIs will be conducted through the Framework Analysis approach. Framework analysis is becoming a popular approach in qualitative research within clinical trials. It was developed in the 1980's by UK social science researchers and has been used extensively for applied or policy relevant qualitative research. Framework analysis provides a highly systematic method of categorizing and organizing data according to key themes, concepts and emergent categories in grids or matrices. The best aspect of using framework analysis is that it provides an opportunity to link qualitative findings with those of quantitative research. This will be relevant in comparing, contrasting and enhancing findings collected quantitatively, thus increase the validity of findings by using triangulation methods. Data analyses will be undertaken by trained research team members experienced in qualitative data analyses. The research team will be trained on the process of framework analysis by a qualified social science researcher, to ensure a consistent approach to analysis.

Each transcript will be coded by at least two researchers at each research site and assessed for consistency in coding. Any disagreements about the codes will be brought to the research team and discussed until agreement is reached.

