### **Randomised trial**

A total of 144 eligible individuals (72 per country: South Africa and Uganda) will be initially approached and consented as described in Section 6.3. If eligible, they will be randomised in equal numbers to one of 9 treatment arms, each comprising a total of 16 evaluable participants, 8 per country. Four treatment arms will receive FTC-TDF (two dosing schedules, two timing schedules), four arms will receive FTC-TAF (schedules the same as for FTC-TDF) and one group will be the control group who will receive no PrEP (Figure 1, Table 1).

According to randomisation arm, circumcision will either be five or 21 hours after the last dose of PrEP has been given. Participants will take tablets at each clinic site under directly observed therapy (DOT).

Participants in the control arm will have their circumcision soon after randomisation, they will not have to wait for five hours. At the appropriate time after dosing, all other participants receiving PrEP will undergo VMMC. Their foreskins will be collected, and transferred to the local lab within two hours of circumcision. At the lab, foreskins will be processed and used for the explant HIV-

infection models. Local scientists trained by Imperial College staff from the UK will conduct experiments. Protection from HIV infection will be determined by ex vivo challenge using wild type HIV virus on freshly resected foreskins. Participants who do not take their full course of treatment, or choose to delay circumcision will be deemed to be un-evaluable and will be replaced. We will randomise a maximum of 100 consenting men to obtain 72 evaluable participants.

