| SAE monitoring                                                      |           |               | X           | X                                 | X         |
| Conmeds                                                             | X         |               | X           | X                                 | X         |
| RPR                                                                 |           |               |             | X                                 |           |
| Urine
- STI screen (first-catch sample
- Research (mid stream |           |               |             | X                                 |           |
| Research Blood - PBMCs for PK/PD - Plasma for cytokines and PK      |           | X             |             | X                                 |           |
| Research rectal swab x1                                             |           |               |             | X                                 |           |
| Research urethral swab x1                                           |           |               |             | X                                 |           |
| Research glans microbiome swab x 1                                  |           |               |             | X                                 |           |
| Post - operative review                                             |           |               |             |                                   | X         |
| Exit survey                                                         |           |               |             |                                   | X         |
| Exit in-depth interview                                             |           |               |             |                                   | X         |

\*randomisation will take place after eligibility has been confirmed

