### **Adverse Event Reporting**

Symptoms or conditions that occur prior to randomisation will be recorded in the participant's medical history as pre-existing conditions. All new or worsening symptoms or conditions that occur following randomisation will be considered AEs and will be recorded on the AE CRF regardless of severity and relationship to study product. AEs that are ongoing at the time of study exit will be followed up for up to 30 days after study exit and then, if not resolved, will

be referred to a health care provider for further follow-up. After this period sites must report serious, unexpected, clinical suspected adverse drug reactions if the study site becomes aware of the event on a passive basis, i.e., from publicly available information.

Study staff will document in source documents and the appropriate CRF AEs reported by or observed in enrolled study participants regardless of severity and presumed relationship to study product. Relatedness is an assessment made by a study clinician of whether or not the event is related to the

study agent. The relationship of all AEs to study product will be assessed as either related or not related.

AE severity will be graded according to the grading table. (eg. DAIDS grading table) This version will be used for the entire duration of the study. For this study, all Grade 3 or above events or reactions will be reported as adverse events.

Sites may be required to submit AE and SAE information to local regulatory agencies or other local authorities per in country guidelines.

Study participants will be provided with contact telephone numbers to report any AEs they may experience, except for life-threatening events, for which they will be instructed to seek immediate emergency care.

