## **8.5 Treatment Stopping Rules**

The trial may be prematurely discontinued by the Sponsor, Chief Investigator, ethics committee or

Regulatory Authority based on new safety information. If the study is prematurely discontinued, active participants will be informed and no further participant data will be collected.

We do not expect any serious adverse events from ARV received during the study- participants receive a maximum of three doses of PrEP only. However, if a participant experiences side effects the drug can be withdrawn at any time. If the drug is stopped prematurely then the participant will be withdrawn from the study and replaced.

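### Section 9.2 limits analysis to men with a foreskin sample, so men who stop PrEP for side effects could go uncounted, and the adverse event capture rules conflict

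*Protocol*

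**What the plan says.** **Who is analysed.** Protocol section 9.2 opens with "Only men who provided a foreskin sample will be included in analysis". The same section goes on to demographic, clinical and survey summaries, none of which needs tissue.

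**Who leaves before giving a sample.** Section 8.5 allows drug to be withdrawn for side effects and adds: "If the drug is stopped prematurely then the participant will be withdrawn from the study and replaced". Section 4.2 (Randomised trial) has the matching rule: "Participants who do not take their full course of treatment, or choose to delay circumcision will be deemed to be un-evaluable and will be replaced". It also sets a recruitment ceiling: "We will randomise a maximum of 100 consenting men to obtain 72 evaluable participants".

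**What is captured.** Section 8.4 (Adverse Event Reporting) says "All new or worsening symptoms or conditions that occur following randomisation will be considered AEs" and sends them to the adverse event form whatever their severity. Later in the same subsection it says "For this study, all Grade 3 or above events or reactions will be reported as adverse events". Sections 7.1.3, 7.1.4 and 7.1.5 each call for an adverse event review at the visit. The row in Tables 3.1 to 3.5 is labelled "SAE monitoring", and no table has a row for non-serious events.

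**The concern.** Two separate problems bear on tolerability.

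First, the analysis rule selects on something close to the outcome. A man who takes a first dose, has a side effect and stops is withdrawn under section 8.5, gives no foreskin, and is excluded by section 9.2. He is excluded because he did not tolerate the drug, and his replacement is someone who completed the course. PrEP acceptability, a stated secondary objective, is also exposed: the exit survey is given at the circumcision visit or the final visit, which a man withdrawn earlier may never reach.

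Second, sites are given different instructions on what to collect. The common reactions listed in section 5.3, such as nausea, vomiting and headache, can be low grade. A site working from the visit table and the Grade 3 sentence could omit them, while a site working from the all-severity sentence would record them. Events never collected cannot be recovered at analysis, whatever an analysis plan says.

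**Working it through.** **1. The plan's own figures.** 9 arms × 16 = 144 evaluable men, and 2 × 16 = 32 per pooled group. Both agree with section 9.1. No alpha, power or effect size is stated and the analyses are descriptive, so no power calculation is affected.

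**2. The recruitment ceiling.** 100 − 72 = 28 men, or 28%, may be randomised and not count as evaluable. Since 72 is the per-country number, the ceiling is apparently per country, giving 2 × 28 = 56 of 200 overall. This is a maximum for every cause: an incomplete course or delayed circumcision (section 4.2), loss to follow-up or laboratory need (section 6.4), and missed windows (section 6.5). It is not a rate of stopping for side effects.

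**3. Where stopping drug can occur.** In Table 1, arms 2, 3, 6 and 7 have one dosing occasion, and section 5.2 has both tablets taken together, so nothing remains to be stopped. In those arms a side effect can remove a man only if he withdraws or misses his circumcision window. Arms 4, 5, 8 and 9 have a second dose. The section 8.5 rule can therefore act only in 4 × 16 = 64 evaluable places, which are pooled groups B and D.

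**4. Range of effect under assumed rates.** The protocol gives no stopping rate. Let q be the assumed share of men starting a 2+1 course who stop for an adverse event, and a the assumed share of completers with any adverse event.

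- Chance of at least one such stop among 64 starters: 1 − (1 − q)^64
- Men dropped while filling 64 places: 64/(1 − q) − 64
- Any-event proportion in all dosed men: q + (1 − q)a, so the shortfall among completers alone is q(1 − a)

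| q (assumed) | Chance of at least one stop | Men dropped | Any-event proportion in all dosed men, if a = 10% |
|---|---|---|---|
| 1% | 47% | 0.6 | 10.9% |
| 2% | 73% | 1.3 | 11.8% |
| 5% | 96% | 3.4 | 14.5% |
| 10% | 99.9% | 7.1 | 19.0% |

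With a anywhere from 5% to 20%, the shortfall is 0.8 to 0.95 percentage points at q = 1% and 8 to 9.5 points at q = 10%.

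**5. The capture rules side by side.**

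| Place | What is captured |
|---|---|
| Section 8.4, first statement | All new or worsening conditions, any severity |
| Section 8.4, later statement | Grade 3 or above, reported as adverse events |
| Sections 7.1.3 to 7.1.5 | Adverse event review |
| Tables 3.1 to 3.5 | Serious adverse event monitoring only |

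The second line may be meant as a reporting threshold rather than a recording threshold, but nothing in the text marks it as one.

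**The case against.** The strongest reply is that no safety estimate is specified that could be biased. Safety and tolerability are not among the objectives or endpoints in section 4.1, section 9 describes no adverse event analysis, and a safety population is normally left to a statistical analysis plan, which is not at hand. The 9.2 sentence also leads into the explant analysis, where a foreskin is indispensable. Data on withdrawn men are not discarded: adverse events are recorded from randomisation (section 8.4), the reason for withdrawal and any causative event go on the case report form, permission is sought to use data collected before withdrawal (section 6.5), and the IDMC reviews safety and sees data by randomised group (section 13). On capture, section 8.4 states the any-severity rule more than once, and a table row is only a label.

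Much of this stands. It removes any claim that bias is built in, and the absence of a safety set is not itself the fault. Two things survive. The 9.2 sentence is a stated rule without exception, and it heads summaries that need no tissue; a safety set in an analysis plan would contradict it. And the capture conflict governs what sites write down, which an analysis plan cannot repair.

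**Conclusion.** The point holds as two wording defects with a possible, unquantified consequence. Read literally, sections 4.2, 8.5 and 9.2 together exclude men who were dosed and stopped before circumcision for an adverse event, so tolerability may be understated, with any bias tending to favour the 2+1 regimens. The inconsistent capture rules could lose lower-grade events, depending on which text a site follows.

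A reader might infer more than the protocol supports:

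- **That tolerability is understated.** No tolerability analysis is specified, and events in withdrawn men are still recorded.
- **That 28% of randomised men fall outside every analysis.** That figure is an all-cause ceiling, and reading it as per country is an inference. Men replaced for laboratory need may have given a foreskin, and men outside a window may be re-dosed after washout and stay in.
- **That every PrEP arm is equally exposed.** The drug-stopping route exists only in arms 4, 5, 8 and 9.

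The size rests wholly on assumed stopping rates. With at most three tablets per man and few events expected, the low end of the range is plausible, but the protocol does not establish it. Severity is minor to moderate: the primary endpoint and sample size are unaffected.

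**What to change.** 1. In section 9.2, limit the foreskin-sample sentence to the ex vivo and tissue endpoints.
2. In the same section, state that adverse events, discontinuations and replacements are summarised by arm for all men who took at least one dose, plus arm 1 from randomisation, subject to the data-use permission in section 6.5.
3. Reconcile section 8.4, sections 7.1.3 to 7.1.5 and Tables 3.1 to 3.5 to one capture rule. If the Grade 3 sentence is meant as a separate reporting rule, label it as such, and rename the table row to match the chosen rule.

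The cost is wording and one extra descriptive table. Under the any-severity rule in section 8.4 the data should already be collected from randomisation; the third change makes sure that they are. The target of 144 evaluable men does not change.

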### **Ex vivo challenge validation**

Part of the purpose of this study is to empower research sites. Therefore, after appropriate training, mentorship and site preparation, the ex vivo model will have to be validated at each site in order to progress to the main study. Three men will be recruited at a time. These individuals will not be randomised and will not receive PrEP prior to VMMC. Their foreskin tissue will be exposed to HIV through the ex vivo challenge. Successful infection of the excised foreskin tissue of at least three consecutive men using ex vivo challenge is required to validate the site. A maximum total sample size of 12 men will be recruited for validating the methods.

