#### **6.4 Randomisation Procedure**

Enrolled participants will be randomized prospectively into one of 9 groups in equal ratios, stratified by country (n=144; 8 participants per group per country). Randomisation will be performed separately in each country, each using blocks of size 9 and 18, so that one or two men in each block will be assigned to each of the nine groups. The randomisation schedule will be assigned in London by the trial statistician. The trial statistician will send lists to each country to be pre-prepared into consecutive sealed randomisation envelopes with country and study ID's printed on the outside and containing the allocated trial arm. After a participant is successfully screened, the next envelope will be opened, and the man allocated to the appropriate trial arm. This is not a blinded study therefore participants and research team will know which medications the patient is receiving.

When the intended number of randomisations have been performed, some groups may be incomplete due to withdrawals, lost to follow-up, or laboratory need. At this stage a new randomisation list will be drawn up (by the trial statistician) and men will be recruited to reach the intended sample size for each arm. By adding men at this stage, it will be possible to maintain allocation concealment.

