## **7.4 End point Sample Analysis**

**a. Ex vivo challenge of foreskin tissue and PBMCs**

Quantification of protection from HIV-1 infection in foreskin tissue and PBMCs will be initially carried out in local laboratories. In brief, foreskin explants will be challenged or not (for negative background control tests) *ex vivo* with HIV-1BaL at two titers; a high titer normally used in pre-clinical assays in the laboratory and a low titer trying to mimic *in vivo* levels. *Ex vivo* challenge will be performed using a non-polarized system by submerging the tissue explant in 200 µl of

virus diluted at the appropriate titer. Following 2 h of incubation, explants will be washed with PBS to remove unbound virus and transferred to a fresh culture plate. Tissue explants will then be cultured for 15 days and maintained by harvesting approximately two-thirds of culture supernatant at days 3, 7, 11 and 15, and refeeding the cultures with fresh medium. The extent of virus replication in tissue explants will be determined by measuring the p24 antigen concentration for HIV-1 in supernatants at each harvest time point with antigen-specific ELISA. The supernatant fluid collected from the culture supernatants will be stored and subsequently analysed for HIV infection at Imperial College London. Interim analyses after 30% and 60% recruitment will confirm continued validation of assays and whether recruitment needs to be extended in any arm.

*Ex vivo* dosing of foreskin explants with FTC-TDF or FTC-TAF will be used to i) mimic the postcoitus dosing in the IPERGAY trial; and ii) evaluate the time frame for initiating PEP with FTC- TDF or FTC-TAF. In the first case, to mimic IPERGAY, foreskin samples obtained from CHAPS participant who will have received one or two pills of FTC-TDF or FTC-TAF, will be dosed by submerging the explant in 200ul of drug diluted at the appropriate concentration, 18hrs after *ex vivo* viral challenge.

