## **9. Statistics**

### **9.1 Sample Size**

The total evaluable sample size will be 144 men; 72 in each country. For the primary comparison, data from both countries will be combined, as will the two groups where men receive the same PrEP drug and dose and differ only in timing of PrEP dose prior to circumcision. Comparisons will therefore be between 32 individuals in each treatment group. The study is not powered to detect a difference between these four treatment groups.

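### The primary comparison combines the two countries with no country-stratified estimate and no by-country p24 result, although randomisation is stratified by country and each country runs its own explant laboratory

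*Protocol*

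**What the plan says.** **Design.** Protocol section 6.4 has men "randomized prospectively into one of 9 groups in equal ratios, stratified by country", with 8 men per arm in each country. It adds: "Randomisation will be performed separately in each country, each using blocks of size 9 and 18". Country is the only stratification factor stated.

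**Laboratories.** Under the ex vivo challenge validation heading of section 4.2, "the ex vivo model will have to be validated at each site in order to progress to the main study". Foreskins go to the local laboratory, where local scientists trained by one UK institution run the experiments (section 4.2, Randomised trial). Section 7.4(a) adds: "Quantification of protection from HIV-1 infection in foreskin tissue and PBMCs will be initially carried out in local laboratories". Stored culture supernatants are later analysed at one central laboratory.

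**Analysis.** Section 9.1 says: "For the primary comparison, data from both countries will be combined". Section 9.2 repeats this, defining the primary groups "as indicated in Figure 1 (Groups A, B, C, D), pooled across the two sites". The analysis is descriptive, and results are to be reported by group with 95% confidence intervals. That last sentence closes the in vitro dosing paragraph but is worded to cover all analysis. Tabulation by country is promised for demographic and clinical characteristics and survey responses, not for the p24 outcomes.

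**The concern.** The design treats country as worth controlling: separate randomisation lists, separate laboratories, separate validation. The primary analysis then makes no use of it. Three things are at stake.

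- **Precision.** If the chance of non-infection, or the p24 level, differs between sites, that difference is left in the error term. The pooled interval is then wider than the design requires, with only 32 men per group.
- **A concealed site difference.** The primary endpoint is non-infection. A laboratory whose challenge takes poorly will show non-infected tissue whatever drug was given, and this looks like protection. Group X is there partly to show that the challenge works, but it has 8 men per country. If only the combined 16 are shown, a weak site can be masked by a good one.
- **Balance.** The even split by country is planned but depends on replacement. Up to 100 men may be randomised to obtain 72 evaluable (section 4.2), incomplete arms are refilled from a new list (section 6.4), and recruitment may be extended in any arm after the interim looks (section 7.4). A pooled contrast has no protection if a group ends with an uneven country mix.

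**Working it through.** **1. The plan's own figures.** 9 arms x 8 men x 2 countries = 144. Each pooled group is 2 timings x 8 men x 2 countries = 32, that is, 16 per country. Both agree with section 9.1. No alpha, power, effect size or standard deviation is given, so there is no power figure to reproduce.

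**2. Bias under the planned balance.** Each group takes half its men from each country, so a country effect cancels from the difference between two groups. The bias is 0.

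**3. Interval width, binary endpoint.** The protocol gives no non-infection rate by country, so a range is assumed. Let the rates be p1 and p2, taken as equal in the two groups compared, with mean p.

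- Pooled SE of the difference = sqrt(2 x p(1-p)/32)
- Stratified SE = sqrt(2 x v/32), where v is the mean of p1(1-p1) and p2(1-p2)

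| Assumed rates by country | p(1-p) | v | Pooled SE | Stratified SE | Ratio |
|---|---|---|---|---|---|
| 50% v 70% | 0.24 | 0.23 | 0.1225 | 0.1199 | 1.02 |
| 30% v 70% | 0.25 | 0.21 | 0.1250 | 0.1146 | 1.09 |
| 20% v 80% | 0.25 | 0.16 | 0.1250 | 0.1000 | 1.25 |

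The pooled interval is thus about 2%, 9% and 25% wider than the stratified one.

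**4. Interval width, continuous p24 outcomes.** Let the countries differ by d within-country standard deviations (also assumed). With 16 men per country in a group of 32, the expected pooled within-group variance is 1 + 8d²/31, against 1 within country. The square root is 1.03 for d = 0.5, 1.12 for d = 1 and 1.43 for d = 2. Simulation (40,000 runs per value of d) gave the same width ratios. Coverage of the pooled nominal 95% interval was 95.6%, 97.2% and 99.5%; the country-adjusted interval stayed at about 95%.

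**5. Shift if balance is lost.** The shift is the difference in country share times the site difference, here assumed to be 40 points.

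- One arm at 10:6 and its partner at 8:8 make the group 18:14. Shift = (18/32 - 16/32) x 40 = 2.5 points.
- Groups at 18:14 and 14:18. Shift of the contrast = (18/32 - 14/32) x 40 = 5 points.

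**The case against.** The best reply is that pooling says only whose data form groups A to D. A stratified estimate also combines both countries, no model is specified, and a statistical analysis plan that is not shown could add a country term without contradicting the protocol. This stands in part: sections 9.1 and 9.2 do not forbid stratification. But the combination is written twice and by-country reporting is promised for other variables only, so the point does not rest on silence alone.

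A reader might also infer that country is the main driver of explant infectivity. The protocol has no infectivity data by country and does not rank such factors. Several provisions reduce a laboratory effect: common training, validation on at least three consecutive men, assay checks at 30% and 60% recruitment, and central analysis of stored supernatants. They do not remove differences in transport, challenge or culture.

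The imbalance case runs against the stated target of 8 per arm per country, and refilling aims to restore the intended numbers. This is fair: step 5 shows what happens if the target is missed, not what is expected.

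Finally, with 16 men per group per country and rates near 0% or 100%, a simple Mantel-Haenszel variance can shrink toward zero. That bears on the choice of interval, not on whether to stratify.

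**Conclusion.** The point holds, at moderate importance. A factor built into the randomisation, and tied to where the tissue is challenged and cultured, is absent from the primary analysis as written.

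A reader might infer that the pooled result is biased or that false positive findings become more likely. The documents do not support that. Under the planned balance there is no bias, and the interval errs on the wide side. The loss is precision, negligible if the sites are alike and up to about 25% in interval width at the most extreme assumed binary gap. A possible site difference also goes unreported. A shift of 2.5 to 5 points arises only if replacement leaves an uneven country mix and the sites differ by 40 points.

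All these sizes rest on assumed site differences. Section 9.1 states that the trial is not powered between the four groups and section 9.2 makes the analysis descriptive, so no formal decision depends on the interval.

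**What to change.** In sections 9.1 and 9.2, keep both countries in groups A to D and state that:

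1. contrasts in non-infection are estimated as a risk difference stratified by country, with a score-type interval suited to small or zero cells;
2. comparisons of p24 level at day 15, slope and area under the curve include a country term;
3. group X infection and the A to D results are also shown by country, descriptively.

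This is a change of wording. Country is already recorded for every man, and the sample size stays at 144.
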